## Abstract

**Background:**

Excessive sedentary time has been negatively associated with several health outcomes, and physical activity alone does not seem to fully counteract these consequences. This panorama emphasizes the essential of sedentary time interruption programs. “The Up Project” seeks to assess the effectiveness of two interventions, one incorporating active breaks led by a professional and the other utilizing a computer application (self-led), of both equivalent duration and intensity. These interventions will be compared with a control group to evaluate their impact on physical activity levels, sedentary time, stress perception, occupational pain, and cardiometabolic risk factors among office workers.

**Methods:**

This quasi-experimental study includes 60 desk-based workers from universities and educational institutes in Valparaiso, Chile, assigned to three groups: (a) booster breaks led by professionals, (b) computer prompts that are unled, and (c) a control group. The intervention protocol for both experimental groups will last 12 weeks (only weekdays). The following measurements will be performed at baseline and post-intervention: cardiometabolic risk based on body composition (fat mass, fat-free mass, and bone mass evaluated by DXA), waist circumference, blood pressure, resting heart rate, and handgrip strength. Physical activity and sedentary time will be self-reported and device-based assessed using accelerometry. Questionnaires will be used to determine the perception of stress and occupational pain.

**Discussion:**

Governments worldwide are addressing health issues associated with sedentary behavior, particularly concerning individuals highly exposed to it, such as desk-based workers. Despite implementing certain strategies, there remains a noticeable gap in comprehensive research comparing diverse protocols. For instance, studies that contrast the outcomes of interventions led by professionals with those prompted by computers are scarce. This ongoing project is expected to contribute to evidence-based interventions targeting reduced perceived stress levels and enhancing desk-based employees’ mental and physical well-being. The implications of these findings could have the capacity to lay the groundwork for future public health initiatives and government-funded programs.

## Background

Sedentary behavior is defined as any waking behavior with an energy expenditure of ≤1.5 METs while sitting, reclining, or lying down (1). This behavior has been negatively associated with various health markers, such as, sarcopenia, osteopenia, diabetes, hypertension, metabolic syndrome, cardiovascular disease, overweight, obesity, and stress (2–7). This scenario is even worse in desk-based workers exposed daily to a high amount of sedentary time, decreased work performance, and increased absenteeism which implies unfavorable implications for the worker, company, and society (8). Consequently, interrupting sedentary time with physical activity emerges as a valuable strategy for addressing sedentary behavior (9–11).

In this sense, advocating for workplace programs that promote physical activity and reduce the prolonged time spent in sedentary activities becomes a practical proposition in occupational health (involving both physical and mental aspects of well-being). The World Health Organization characterizes occupational health as a highly interdisciplinary effort to safeguard and enhance workers’ health by preventing and managing work-related diseases and accidents (12). A key point to emphasize is that scientific evidence underscores how certain detrimental health outcomes associated with sedentary behaviors seem to be independent of individuals’ physical activity levels (13). Thus, interventions based on physical activity alone would not be entirely effective in counteracting the adverse effects of sedentary behavior on health (9). In this regard, strategies for reducing sedentary time have been associated with decreased body fat, increased fat-free mass, decreased abdominal fat, resting heart rate, and blood pressure (10, 14–16).

Given the potential hazards associated with prolonged sitting at work and physical inactivity, including increased stress and occupational pain (17–19), it is imperative to examine workplace interventions that can mitigate these behaviors and promote overall health and well-being (20). The literature has mainly proposed two types of active breaks to interrupt sedentary behavior in desk-based workers: “Booster Breaks” (B-B) and “Computer Prompts” (C-P) (21–23). On the one hand, B-B can be defined as guided, programmed, and performed active breaks in the workplace, with an average duration around of 15 min (21). This type of break benefits individuals’ physical and mental health by reducing stress, improving social interactions at work, increasing physical activity levels, and decreasing body mass index (BMI) (21, 22). On the other hand, C-P is characterized by unguided breaks performed through the software on the work computer, with a short duration (e.g., 2–3 min), accumulating around 15 min during the whole working day (21). Two systematic reviews with meta-analyses have concluded that this type of break can reduce sedentary behavior and increase physical activity levels, but the body of evidence comparing B-B and C-P is still limited (23, 24).

Most of the research on workplace interventions to reduce sedentary behavior has been conducted in high-income developed countries (21, 23, 25). In Latin America there is very little information on this topic, specifically in Chile, to our knowledge there are no previous studies on strategies to reduce sedentary time at work. However, previous research indicates that in 2016, 35.9% of the Chilean adult population spent more than 4 h in sedentary time (26). Thereby, the current project intends to fill gaps in the existing literature on this topic in an under-researched geographical world region. First, previous studies investigating B-B and C-P protocol parameters used physical activity questionnaires, pedometers, BMI, and waist circumference measures to analyze physical activity levels and body composition, respectively, (21, 23). However, to date, scarce evidence has evaluated movement behavior by accelerometry and dual-energy X-ray absorptiometry (DXA) to accurately measure participants’ body composition using the same protocol. DXA provides comprehensive body composition assessment, including fat mass, lean mass, and bone mineral density, for a more accurate portrayal of participants’ health (27, 28). Accelerometry delivers precise, device-based measurements, revealing daily movement patterns with minimal reliance on self-reporting (29).

Second, this study introduces an innovative approach by contrasting two types of interventions (B-B and C-P), which will be equivalent in duration and intensity. However, these interventions differ in their structures. B-B will be conducted continuously for 14–16 min, while C-P will consist of brief 2-min breaks scattered throughout the 8-h workday (averaging 14–16 min). By assessing the differentiated effects of these breaks, we aimed to identify effective strategies to improve the health of office workers.

Third, previous scientific evidence has shown that diverse variables can affect our main outcomes, encompassing factors such as sleep time and quality, socioeconomic status, smoking, and eating habits (30–32). Consequently, it is imperative to explore these interrelated factors using a more comprehensive approach (33). Initially, these variables will be used as covariates to explore their influence on study outcomes.

Finally, it is crucial to take public health measures to contribute to the reduction of sedentary behaviors in workers. Thus, we anticipate that our findings could contribute to the formulation of evidence-based interventions that can be deployed or not to improve the health and well-being of this population.

Therefore, this manuscript aims to describe the design and methods of “The Up Project,” which seeks to establish the efficacy and differences between two interventions addressed for interrupting sedentary time in desk-based workers. The principal outcomes will include variations in cardiometabolic risk factors, sedentary and physical activity levels, perception of stress, and occupational pain. Accordingly, our primary hypothesis is that both intervention groups will yield better results compared to the control group. However, we expect no discernible differences between the intervention groups due to their equivalence in duration and intensity. This is mainly because previous studies suggest that varying the frequency of breaks can improve cardiometabolic risk markers. However, studies comparing different frequencies at the same intensity and volume are lacking (34–36). In this sense, previous literature suggests that when exercise or physical activity volume and intensity are kept constant, frequency does not significantly impact muscle mass or cardiovascular risk (37, 38).

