#### Procedures

The project will be conducted in three stages, comprising two visits to the Physical Performance and Health Laboratory of the PUCV (stage one and stage three) and one visit to the participants’ offices (stage two). Previous to measurement sessions, participants will be asked not to consume any type of stimulant prior to the measurements (such as caffeine or tea, mainly for blood pressure and heart rate). The first stage will consist of a pre-intervention measurement session in our laboratory, in which cardiometabolic risk factors, stress perception, occupational pain, physical activity, sedentary time at work, 24-h behavior, eating and smoking habits, and sociodemographic information will be evaluated. In addition, participants will be given an accelerometer, which will be removed 7 days later, and the intervention will begin once the accelerometer is removed. The intervention will have a total duration of 12 weeks, because previous literature indicates that 12 weeks is sufficient time to observe behavioral changes that can be extended beyond the time of the intervention (44). In the second stage (sixth week of intervention), the three groups will receive accelerometers to re-evaluate their daily physical activity intensity, sedentary time, and breaks in sedentary time. Finally, the third stage (post-intervention measurement) will consist of a second visit to our laboratory, where all variables will be re-evaluated. The anonymized and raw data obtained will be made available by the corresponding author upon reasonable request. A diagram of the study design, sample, and measures is presented in Figure 1.

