#### Physical activity, sedentary time, and sleep time

An ActiGraph GT3X + accelerometer (ActiGraph, Illinois, United States) will be utilized for device-based measurement to monitor physical activity, sedentary behavior, and sleep time. The accelerometer has been validated for assessing physical activity, sedentary behavior, and sleep quality (48, 49).

Participants will be instructed to continuously wear the device on their non-dominant wrist for 7 days (24 h/day) and only remove it for water activities. Wrist-worn accelerometers have become popular because they place a low burden on participants and provide valid and reliable measurements of physical activity (50). Accelerometers will be initialized to a sampling rate of 100 Hz and downloaded using ActiLife^®^ software (ActiGraph, Pensacola, FL). The raw accelerometer data (.gt3x) will be processed using the GGIR 3.0–5 package (51), in R studio. The minimum amount of accelerometer data that will be considered acceptable will be 600 min of valid daily monitor wear on at least 4 days including a weekend day (52, 53). The MVPA threshold and cutoff points used will be those proposed by Hildebrand et al. (54, 55). Sleep time (periods without z-angle changes of >5° for at least 5 min) will be calculated using an algorithm proposed by van Hees et al. (56), and identification of onset and wake time will be guided by the HDCZA algorithm (51). All participants start with their pre-intervention and post-intervention measurements on the same dates, in order to maintain the same measurement conditions for all and reduce the risk of bias.

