#### Other measurements (covariates)

Previous studies have established that cardiometabolic risk factors are not only affected by body composition, physical activity, or sedentary behavior but can also be influenced by various healthy lifestyle habits (30–32). Therefore, we identified a series of related factors that will be included as covariates in our statistical analyses to assess their impact on our outcomes.

We will use an ActiGraph accelerometer to measure sleep quality (48, 49). This variable plays a fundamental role in cardiovascular health (68). Lack of quality sleep can increase blood pressure and inflammation by increasing cortisol levels and decreasing immunity, elevating the risk factors for cardiovascular problems (68).

The questionnaire on adherence to the Mediterranean diet will be applied to assess eating habits, specifically designed to measure participants’ adherence to it and determine its relationship with cardiometabolic factors (69–71). This questionnaire gathers information on the frequency of consumption of foods characteristic of the Mediterranean diet using a Likert scale format. To assess participant adherence, the score of each question is summed to obtain a total score, reflecting the individual’s adherence to the Mediterranean diet.

The Fargerstörm test, which scores various aspects of smoking habits on a Likert scale and enables us to determine the level of dependence on this substance, will be used to assess smoking habits (72).

Furthermore, we will obtain information on the participants’ socioeconomic status using a questionnaire on the distribution and average autonomous income of households by income deciles. This questionnaire provides essential data on the *per capita* income of the participants and follows the guidelines of the “Asesoría Técnica Parlamentaria” of the Chilean government (73). In addition, the educational level and occupational status of the participants will also be recorded. These measures are considered relevant as predictive cardiometabolic risk factors (70, 74, 75). In addition, sociodemographic questions will be asked to characterize the study sample.

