In parallel, sensitivity analyses will be performed according to the intention-to-treat principle. All analysis models will also adjust for relevant covariates such as sex, age, socioeconomic status, eating habits, smoking habits among others depending on their relevance in the model studied. To determine which variables are appropriate to use as covariates, directed acyclic graphs will be explored. These graphs are built on the expert knowledge of the researcher, which would facilitate the causal understanding of the phenomenon and the type of linkage between the variables involved, minimizing the introduction of bias during the design of the study and in the analysis of results (80, 81). All analyses will be performed in different software according to the needs of the researchers (e.g., R Studio, Jamovi, SPSS).

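### Sleep, socioeconomic status, smoking and diet are to be entered as covariates to show their own influence on the outcomes, which coefficients from a model built for the intervention effect do not show

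*Protocol article*

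**What the plan says.** The Background lists variables that may affect the main outcomes, "encompassing factors such as sleep time and quality, socioeconomic status, smoking, and eating habits", calls them interrelated, and presents exploring them as the third gap that the study will fill. It continues: "Initially, these variables will be used as covariates to explore their influence on study outcomes". The Methods section Other measurements (covariates) describes factors "that will be included as covariates in our statistical analyses to assess their impact on our outcomes" and covers accelerometer sleep quality, Mediterranean-diet adherence, smoking dependence and socioeconomic status.

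Two other places give such variables a different job. The Data analysis plan states: "All analysis models will also adjust for relevant covariates". It names sex, age, socioeconomic status, eating and smoking habits as examples, leaves the list open, and has directed acyclic graphs decide which variables are suitable. The strengths paragraph of the Discussion says the covariates serve to adjust the model when the intervention's effects are explored.

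On sleep, the section Physical activity, sedentary time, and sleep time says one accelerometer "will be utilized for device-based measurement to monitor physical activity, sedentary behavior, and sleep time", worn 24 h a day for 7 days. Procedures describes a post-intervention visit "where all variables will be re-evaluated".

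**The concern.** An adjustment set is chosen for one exposure. A set that removes confounding of the comparison between breaks and control does nothing in particular for the confounding of smoking or of socioeconomic status, and it may hold fixed the variables through which they act. Socioeconomic status adjusted for diet and smoking is at best a direct effect. That the factors are interrelated, as the Background says, is the condition under which mutually adjusted coefficients mislead.

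At stake is what is published beside the main result: lifestyle impacts read off mutually adjusted terms, from about 54 completers (60 less the planned 10% loss), in a project meant to inform public policy. This can happen even when the intervention estimate is sound.

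Sleep raises a second, conditional matter. It is named as a covariate, comes from the same record as the sedentary and activity outcomes, and is measured again after the intervention starts. Adjusting those outcomes for follow-up sleep would remove any part of the effect that runs through sleep.

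**Working it through.** The article gives no figure on this point, so there is none to reproduce. All numerical inputs below are assumptions chosen to show the mechanism.

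**1. The stated purposes side by side**

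| Section | Purpose of the covariates |
|---|---|
| Background | explore their influence on outcomes |
| Other measurements (covariates) | assess their impact on outcomes |
| Data analysis plan | adjust the models; set chosen by causal graph |
| Discussion (strengths) | adjust the model for the intervention's effects |

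The first two rows ask about the covariates. The last two ask about the intervention.

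**2. Pathway through other covariates**

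Total effect = direct effect + sum over mediators of (path into mediator × path from mediator). Assume a direct socioeconomic effect of -0.10 SD, with diet and smoking as two equal mediators:

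- paths 0.3 and 0.3: -0.10 - 2(0.09) = -0.28
- paths 0.5 and 0.3: -0.10 - 2(0.15) = -0.40
- paths 0.4 and 0.4: -0.10 - 2(0.16) = -0.42

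With diet and smoking in the model, the coefficient is about -0.10 each time. The share not shown is 0.18/0.28 = 64%, 0.30/0.40 = 75% and 0.32/0.42 = 76%.

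**3. The covariate's own confounding**

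Assume smoking acts directly (0.3) and through diet (-0.5 × -0.4 = 0.2), so its total effect is 0.5. An unmeasured factor raises smoking by 0.6 and the outcome by 0.5. The group effect is -0.5, with group independent of these factors, and residual variances are 1. With group, smoking and diet in the model, the smoking coefficient is 0.3 + (0.5 × 0.6)/(0.6² + 1) = 0.3 + 0.30/1.36 = 0.52. In 400,000 simulated records it was 0.523, and the group effect was -0.497. So the group effect is recovered, while the smoking coefficient is not the direct effect (0.3). It lies near the total (0.5) only because a confounding bias of +0.22 happens to offset the lost 0.20.

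**4. Sleep, if the follow-up value were used**

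Assume an effect of -20 min/day on sedentary time, a sedentary-on-sleep slope of -0.7, and a share of 20 min moving into sleep. Models in 400,000 simulated records, all adjusted for the baseline outcome:

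| Share of 20 min moving to sleep | No sleep term | Baseline sleep | Follow-up sleep |
|---|---|---|---|
| 0% | -20.13 | -20.13 | -20.18 |
| 25% | -19.84 | -19.83 | -17.46 |
| 50% | -20.17 | -20.17 | -15.39 |
| 75% | -19.83 | -19.83 | -12.53 |

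Follow-up sleep removes from nothing to (19.83 - 12.53)/19.83 = 37%. Baseline sleep removes nothing.

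If the day is complete, sedentary = 1440 - sleep - activity. At fixed sleep, the sedentary effect is then minus the activity effect: a 16-min fall with 3 to 8 min going to sleep would be reported as about 13 down to 8 min.

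**The case against.** The strongest reply is that influence and impact are loose words for adjustment. The aims and hypotheses name no covariate effect, no section says that covariate coefficients will be reported, the Discussion states the adjustment purpose, and the Data analysis plan selects covariates by graph according to the model studied. This stands in part: a misreading is invited, not certain. But the purpose appears in both Background and Methods, and the Background lists it among the gaps to be filled. A correct graph for the intervention effect does not turn the other coefficients into effects.

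On sleep the reply largely succeeds. A reader might infer that the plan adjusts sedentary time and activity for sleep from the same follow-up week, and so biases its main comparison. The article does not say so:

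- No section puts follow-up sleep in such a model. The examples in the Data analysis plan do not name sleep, and a properly drawn graph would exclude a variable measured after the intervention started.
- The covariate section names sleep quality ("We will use an ActiGraph accelerometer to measure sleep quality"), which is not a term in the 24-hour sum. Sleep time as a covariate rests on the Background alone.
- The exact identity needs complete days. The article accepts 600 valid minutes a day, so the mirror image is only approximate.
- Mediation and moderation are planned as separate secondary analyses, where follow-up sleep could properly appear.

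Nor should a reader infer from Procedures that every covariate is re-measured. The fuller account under Main variables lists the diet, smoking and socioeconomic questionnaires at stage one only.

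Which wave of a covariate enters is commonly left to an analysis plan, which is not shown, so that silence is no fault. The purpose the article does state for the covariates is a different matter.

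**Conclusion.** The point holds for the stated purpose of the covariates. The Background and the covariate section set a question about each factor's own influence that covariate terms in the intervention models do not answer, and neither the causal graphs nor the adjustment purpose in the Discussion cures this. It does not show that the intervention estimate is wrong.

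The size cannot be fixed from the article. The 64 to 76% loss depends on assumed path coefficients, and with confounding added the error can go either way.

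The sleep matter is a precaution. The loss runs from zero, if the breaks do not change sleep, to about 37% in the most extreme case assumed, and arises only if follow-up sleep is used, which the article does not plan. The change is worth making because it costs almost nothing and prevents published lifestyle impacts that the models cannot support.

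**What to change.** 1. Reword the sentences in the Background and in Other measurements (covariates): these variables, at their pre-intervention values, adjust the intervention effect, and their coefficients are not interpreted.
2. If the impact of a factor is itself a question, fit a separate exploratory model for it, with an adjustment set derived from a graph drawn for that factor.
3. State in the Data analysis plan that only baseline sleep may enter models for device-measured sedentary time and activity. Treat follow-up sleep as an outcome or within the planned mediation analysis.

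The cost is a few sentences, plus some exploratory models if wanted. No new data are needed: sleep is already measured at baseline, and the other questionnaires are completed at stage one.
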